### Intervention

The Hb levels of participants in the intervention group will be taken once a month with a Veri Q® haemoglobinometer, that showed good performance data, in accuracy test compared with the reference value from Nihon Kohden MEK-6420 (R2 = 0.9881) and with the Sysmax reference value (R2 = 0.9968) [21]. If a patient’s haemoglobin level falls below their reference value, the nurse case manager will activate the transfusion circuit by scheduling an urgent referral to the day hospital, an outpatient service where short-term treatment and diagnostic tests are performed. The interdisciplinary team at this unit will prescribe and administer the transfusion and handle the hospital discharge, in a specific circuit between health levels created to this intervention.

The WHOQOL-BREF questionnaire on quality of life will be administered at the first visit and six and 12 months.

To know the satisfaction with the intervention, a single item survey will be administered upon inclusion in the study and six and 12 months. The question is “to what extent are you satisfied with your anemia control”, and the possible answers are not satisfied, satisfied and very satisfied.

An ad hoc satisfaction survey on the intervention will be administered upon inclusion in the study and six and 12 months.

Participants in the control group received standard monitoring, the frequency of which is variable, since it is determined by clinical criteria. The data will be collected by reviewing patients’ computerized clinical records and a bimonthly phone call to determine how many times they have been hospitalized and visited the A&E during the study period. The WHOQOL-BREF questionnaire on quality of life will be administered at the first visit and six and 12 months of inclusion in the study. Data will also be collected for the control group.

### Criteria for suspending or modifying the interventions assigned to each subject in the trial

Participants can leave the study at any time and may withdraw consent.

They will be excluded from the trial in the following cases:Death.They wish to leave the study.Palliative care is initiated and transfusions are rejected.

During the trial, patients in the control group may not have their capillary Hb levels measured.

No risks are anticipated for patients by participation in this study.

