### Main objective

Compare the number of hospitalizations due to anaemia of patients receiving monthly capillary Hb measurements and those receiving standard venipuncture monitoring.

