### Statistical analysis

Statistical analyses will be conducted on a blinded intention-to-treat basis, with all participants who were initially randomised into the study included where data are available for each measurement time point.

Univariate descriptive statistics:

The main numerical variables will be described by measures of centrality and dispersion or absolute and relative frequencies in the case of categorical variables. Univariate comparisons between the intervention group and control group will be performed using mean comparison tests (T-test or similar) or distribution comparison tests (Chi-squared or similar).

Predictive model:

The result variables will be considered discrete quantitative variables. Multiple linear regression will be used to model the data collected, taking those that present significant differences in the previously calculated univariate models as independent variables, in addition to the demographic and clinical variables considered relevant.

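### The exit rule for death and palliative care does not separate stopping the intervention from leaving follow-up or the analysis, and the planned comparison of raw admission counts ignores observed time

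*Protocol article*

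**What the plan says.** The section headed "Criteria for suspending or modifying the interventions assigned to each subject in the trial" lists three exits. The first is introduced by "They will be excluded from the trial in the following cases:Death", the second is the participant's own wish to leave, and the third reads "Palliative care is initiated and transfusions are rejected". The third is a joint condition: both parts must be met.

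The Statistical analysis section states: "Statistical analyses will be conducted on a blinded intention-to-treat basis, with all participants who were initially randomised into the study included". The sentence then carries a qualifier, so that the full rule is "with all participants who were initially randomised into the study included where data are available for each measurement time point". The same section treats the result variables as discrete quantities, compares arms by a t-test or similar (chi-squared or similar for distributions), and models the data by multiple linear regression. Observed time is not mentioned.

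The Main objective is to "Compare the number of hospitalizations due to anaemia of patients receiving monthly capillary Hb measurements" with those under standard monitoring. In the control-group paragraph of the Intervention section, admissions come from "computerized clinical records and a bimonthly phone call to determine how many times they have been hospitalized". For the intervention group, the section on data collection refers to the monthly visits. The length of follow-up is implied by the questionnaires, which "will be administered at the first visit and six and 12 months".

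**The concern.** Three different events are covered by one phrase: the intervention stops, outcome collection stops, or the participant leaves the analysis set. Only the last would breach intention-to-treat outright, but the text does not say which is meant.

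The exits happen after randomisation and are tied to prognosis. The Background links anaemia to mortality in heart failure and chronic obstructive pulmonary disease, and the intervention is meant to reduce decompensation, so exits could plausibly differ by arm. Contact is also monthly in one arm and every two months in the other, so an exit may be noticed sooner in one arm. That last step is inference; the article reports no exits.

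At stake is the main comparison. If exiting patients are dropped, the arms compared are no longer the arms randomised. If their partial counts are kept without observed time, a patient who dies in month 2 with no admission counts the same as one followed for a year with none. In either case a difference in deaths could appear as a difference in admissions.

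**Working it through.** **1. The texts side by side.** The exit section takes participants out of the trial on death or on the palliative-care condition. The Statistical analysis section includes everyone randomised, subject to available data. Nothing says that data before the exit are deleted. Nothing says that they are kept, or that admissions are still collected after palliative care starts. The two sections therefore need to be reconciled.

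**2. The plan's own figure.** Inputs from Sample size: 60% vs 35% hospitalised, two-sided alpha 0.05, power 80%, 10% dropout, arcsine method.
- h = 2·arcsin(√0.60) − 2·arcsin(√0.35) = 0.506
- n = 2·(1.960 + 0.842)² / h² = 61.3, rounded up to 62 per arm
- 62 / 0.90 = 68.9, rounded up to 69 per arm, 138 in total

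The stated size reproduces exactly. The point is about wording and method, not sample size.

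**3. If exiting patients are dropped.** Assumptions: no true effect, 60% admitted in both arms (the control figure in Sample size), 90% of exiting patients admitted, and a fraction q exits. The observed proportion among those left is (0.60 − 0.90·q) / (1 − q).
- q = 10%: (0.60 − 0.09) / 0.90 = 56.7%
- q = 15%: (0.60 − 0.135) / 0.85 = 54.7%
- q = 20%: (0.60 − 0.18) / 0.80 = 52.5%

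| Exits, control vs intervention | Observed, control vs intervention | False difference |
|---|---|---|
| 15% vs 15% | 54.7% vs 54.7% | 0 |
| 15% vs 10% | 54.7% vs 56.7% | 2.0 points |
| 20% vs 10% | 52.5% vs 56.7% | 4.2 points |

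The false difference runs against the arm with fewer exits.

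**4. If shortened counts are kept without time.** Assumptions: 12 months of follow-up, 1 admission per patient-year in both arms, exits at 6 months on average. The mean count is (1 − q)·1 + q·0.5.
- Control, q = 20%: 0.80 + 0.10 = 0.90
- Intervention, q = 10%: 0.90 + 0.05 = 0.95

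The raw means differ although the rates are the same. Mean observed time is also 0.90 and 0.95 years, so admissions per year are 0.90/0.90 = 0.95/0.95 = 1.0, and the difference disappears once time is used.

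**5. Precision, only if exits are lost to the analysis.** Power = Φ(h·√(n/2) − 1.960), with n = 69·(1 − loss).

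| Loss | n per arm | Power |
|---|---|---|
| 10% (planned) | 62.1 | 80.5% |
| 20% (assumed) | 55.2 | 75.8% |
| 30% (assumed) | 48.3 | 70.1% |

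**The case against.** The exit list stands under a heading about interventions, while the analysis population is defined elsewhere and includes everyone randomised. A reader might infer that patients who die or enter palliative care are removed from the analysis and that intention-to-treat is flatly contradicted. The article does not say so, and the heading supports a milder reading in which data up to the exit stay in. Death ends follow-up in any trial, so listing it is no fault in itself. The palliative-care exit is a narrow joint condition, and patients already in palliative care are not enrolled. The data-availability qualifier speaks of measurement time points and fits the questionnaires at least as well as a count over the study period. All of this stands.

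It also stands that bias between arms is not automatic: with no true effect, equal exits from the same risk group give none. The exit rates used above are assumptions, and 2 to 4 points is small beside the 25-point design difference. The power losses do not follow if partial data are kept.

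A further objection is that offsets and the handling of death belong in an analysis plan that is not shown. That would be decisive if the article were silent on method. But it names mean comparison and multiple linear regression on counts, which as described give a shortened count the same standing as a full one. It also ends trial participation for patients who are alive and can still be admitted. These are things the article states, not details it leaves out.

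**Conclusion.** The point holds in a limited form. The exit section and the intention-to-treat statement conflict on their face and should be reconciled. On the milder reading two problems remain: follow-up of the main outcome appears to end for living patients after the palliative-care exit, and raw counts are compared without observed time.

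The size is uncertain because the article gives no rate of death or palliative care. Under the stated assumptions, dropping exits produces a false difference of 0 (equal exits), about 2 points (15% vs 10%) or about 4 points (20% vs 10%). Keeping shortened counts gives means of 0.90 vs 0.95 at 20% vs 10%. Each non-zero figure needs exits that differ between arms; an exit that interacts with treatment could also bias the comparison. It would go too far to say that either reading biases the result, or that the sickest patients are removed from the analysis.

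This should be fixed, but it does not by itself invalidate the trial. Confidence is moderate, because the wording permits more than one reading.

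**What to change.** - Reword the exit section so that these events end study visits or the intervention, and state that no randomised participant is removed from the analysis. The clinical rule for stopping the intervention is not challenged here.
- Collect admissions from clinical records in both arms to 12 months or death, unless consent is withdrawn. The article names records only in the control-group paragraph, so the source must be stated for the intervention arm too.
- Replace linear regression on raw counts with a count model (for example negative binomial) that uses observed time as offset.
- Report deaths by arm, and add a sensitivity analysis of hospitalisation for anaemia or death. The offset corrects for shorter observation but not for exiting patients having a different admission rate, so both are needed.

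The cost is some extra record extraction and a change of model. The sample size of 138 does not change through keeping everyone in the analysis.

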### Statistical analysis

Statistical analyses will be conducted on a blinded intention-to-treat basis, with all participants who were initially randomised into the study included where data are available for each measurement time point.

Univariate descriptive statistics:

The main numerical variables will be described by measures of centrality and dispersion or absolute and relative frequencies in the case of categorical variables. Univariate comparisons between the intervention group and control group will be performed using mean comparison tests (T-test or similar) or distribution comparison tests (Chi-squared or similar).

Predictive model:

The result variables will be considered discrete quantitative variables. Multiple linear regression will be used to model the data collected, taking those that present significant differences in the previously calculated univariate models as independent variables, in addition to the demographic and clinical variables considered relevant.

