#### Data collection, management and analysis

Data will be collected at the monthly visits of participants in the intervention group and the bimonthly visits of participants in the control group.

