### Validity and reliability/rigour

To ensure rigour in the collection of quantitative data, it will be included in a pseudonymized database so that participants cannot be identified, without any additional data, which will be recorded separately using techniques that guarantee it cannot be traced. Data will be stored in a local repository that only the researchers have access to. Participants will be randomly assigned to the groups to avoid any selection bias.

To improve compliance with intervention protocols, the clinical trial supervisor will prepare a report each semester detailing whether or not follow-up visits are being held and properly recorded in the data collection form.

Throughout the trial, if patients who are not in the transfusion circuit are identified, they will be included therein based on the consensus of hospital and primary care professionals.

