### Expected results

#### The main result variables are

Number of hospitalizations due to anaemia.Number of A&E visits due to anaemia.Time elapsed between Hb measurement and circuit activation.Time elapsed between Hb measurement and when the transfusion is performed.Time elapsed between Hb measurement and return home.

The specific measurement variable is the Hb level taken with the Veri-Q® haemoglobinometer once a month.

Other variables are:Satisfaction with monthly anaemia monitoring: taken at six and 12 months. Ad hoc questionnaire.Quality of life: measured at the start of the study and six and 12 months. WHOQOL-BREF questionnaire [22, 23].Prescribed medication that might alter Hb or haematocrit levels.Signs and symptoms of anaemia at monthly visits (dyspnoea, asthenia, palpitations, bleeding, and chest pain).

Socio-demographic and clinical data will be collected from both groups for comparison, including age, sex, educational level, type of anaemia, primary care centre, the physician responsible for monitoring anaemia, cognitive status, inclusion in the case management program, number of haemogram controls performed via venipuncture.

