## Data Availability

Only the Prinicipal Investigator and the clinical trial supervisor have access to the data. The results will be disseminated via peer reviewed publication and conference presentation. This protocol is written according to the SPIRIT guideline.

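### The analysis is called blinded, but the article supports no blinded analyst and leaves the test and covariates to be chosen after the data are seen

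*Protocol article*

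**What the plan says.** All references are to the Protocol article.

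- **Statistical analysis.** "Statistical analyses will be conducted on a blinded intention-to-treat basis". The blinded person and the method are not given. Group comparisons use a t-test, a chi-squared test or an unspecified alternative to either. Multiple linear regression then takes as covariates the variables that differed significantly in the univariate step, plus demographic and clinical variables judged relevant; no list is given.
- **Data Availability.** "Only the Prinicipal Investigator and the clinical trial supervisor have access to the data".
- **Validity and reliability/rigour.** On monitoring: "the clinical trial supervisor will prepare a report each semester detailing whether or not follow-up visits are being held and properly recorded".
- **Data collection, management and analysis.** On the timing of contacts in each arm: "Data will be collected at the monthly visits of participants in the intervention group and the bimonthly visits of participants in the control group".
- **Criteria for suspending or modifying the interventions.** "During the trial, patients in the control group may not have their capillary Hb levels measured".
- **The main result variables.** "The specific measurement variable is the Hb level taken with the Veri-Q® haemoglobinometer once a month".

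**The concern.** Two things meet in one section. First, a property is claimed that the rest of the article does not bear out: on the access rule as written, whoever analyses the data is one of two trial roles, and at least one of them handles arm-specific information during the trial. Second, the analysis to which the claim is attached is not fixed. A reader who takes the word blinded at face value may assume that the choice of test and covariates is protected from knowledge of the result. It is not. The document does not show the blinding, and blinding by label alone would not give that protection in any case. At stake is the credibility of the comparison of hospitalizations, and of the A&E and quality-of-life comparisons analysed in the same way.

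**Working it through.** **The plan's own figure.** Inputs from Sample size: 60% versus 35%, two-sided alpha 0.05, power at least 80%, 10% dropout, arcsine method.

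- h = 2·asin(√0.60) − 2·asin(√0.35) = 0.506
- n = 2·((1.960 + 0.842)/h)² = 61.3, so 62 per arm (power 80.4%)
- 62/0.90 = 68.9, so 69 per arm and 138 in total

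The stated size reproduces. Nothing below changes it. It supplies the 62 evaluable patients per arm used in the simulations.

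**Is a blinded analyst possible on the text as it stands?**

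1. Data Availability admits two roles and no separate statistician. As written, no third person can receive a masked file.
2. The supervisor reports on whether visits are held. Contacts are monthly in one arm and every two months in the other, so judging whether one was missed requires knowing which schedule applies, and hence the arm. This is an inference, but a strong one.
3. For the principal investigator, no section states knowledge of the allocation or says who holds the randomisation list. This stays open.
4. Monthly Veri-Q haemoglobin is a study variable, and capillary measurement is barred in the control arm. In the full data set, a capillary value identifies the intervention arm whatever the label says. The contact schedule does the same.
5. The pseudonymised database described under Validity and reliability/rigour hides identity, not allocation.

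**What can the open choices cost?** Two simulations were run with no treatment effect and 62 per arm. The count distributions and covariate effects are assumptions; the article gives neither.

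*Search over tests and covariate sets* (3,000 runs per setting). Counts had a mean of about 1, either Poisson given the covariates or further overdispersed by a gamma factor with shape 1. There were six candidate covariates, three of them prognostic (log-rate coefficient 0.25). Rejection at 5%:

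| Rule | Poisson | Overdispersed |
|---|---|---|
| t-test alone | 4.5% | 4.6% |
| Mann-Whitney alone | 4.7% | 4.6% |
| Chi-squared (any versus none) alone | 4.6% | 4.7% |
| Smallest p of the three | 7.7% | 8.2% |
| Smallest p, also over eight linear models | 10.7% | 10.6% |

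*Search over all covariate subsets in linear regression* (500 to 1,500 runs per setting). Counts were negative binomial with shape 2, with 4, 6, 6 and 8 covariates and effect parameters 0.3, 0.3, 0.5 and 0.4. Taking the smallest p for arm rejected in 8.8%, 12.6%, 13.8% and 11.8% of runs. With no covariates the rate was 3.7 to 6.4%. That scatter reflects the small number of runs: the standard error at 5% with 500 runs is √(0.05·0.95/500), about 1.0 percentage point.

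**Does coding the arms A/B remove this?** No. Write the model as y = a + b·g + (covariates), with g = 0 or 1. Swapping labels replaces g by 1 − g, which gives y = (a + b) − b·(1 − g) + (covariates). The coefficient changes sign, its standard error does not, and the two-sided p-value is identical. The same holds for two-sided t-test and Mann-Whitney p-values and for the chi-squared test. An analyst who sees only A and B can run the same search and reach the same rejection rate. Coding hides the direction of the effect, not its significance.

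**The case against.** The strongest reply is that a masked analysis is feasible without touching the design. Hospitalization and A&E counts, WHOQOL-BREF scores and baseline variables are collected in both arms, so an extract limited to them could be coded, and a condensed article may leave that procedure to the full protocol. This stands as far as feasibility goes: the documents do not show that blinding is impossible, and the missing procedure alone would be no finding. What remains is a conflict between statements that are in the article: a blinded analysis on one side, and on the other an access rule with nobody outside two trial roles.

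Stronger readings are tempting and should not be adopted:

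- *Everyone with access knows the arms.* A reader might infer this. It is close to certain for the supervisor and plausible for the principal investigator, but stated for neither.
- *Unblinding raises the type I error to 9–14%.* The simulations measure searching among tests and models. As shown, A/B coding leaves that untouched, so the figures cannot be attributed to unblinding.
- *Recruitment could be steered by results seen by arm.* The Discussion ties a wider recruitment region to too few eligible patients, not to outcomes. The approximate closing date under Trial status is an ordinary estimate.
- *The two access rules contradict each other.* Validity and reliability/rigour says: "Data will be stored in a local repository that only the researchers have access to". The researchers may simply be the two roles named in Data Availability.

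**Conclusion.** The point holds in limited form. The word blinded has no support in the article and sits against its access rule, its monitoring arrangement and its data structure. Separately, the choice of test and covariates is left until after the data are seen, with significance as one of the selection rules.

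Only the second part can be given a size: roughly 8 to 14% rejection under no effect, against 5%. That is a worst case of deliberate search under assumed distributions and covariate effects. It is not a prediction, and neither simulation reproduces the plan's own selection rule exactly. The first part misstates the protection in place and has no numerical effect of its own. Neither part invalidates the trial. Both should be corrected before analysis.

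**What to change.** Amend Statistical analysis as follows.

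1. Name one primary test and one covariate list for hospitalizations due to anaemia, and do the same for A&E visits and WHOQOL-BREF. Fix them before any outcome is seen by arm. Remove selection by univariate significance and the open category of relevant variables. The list can be drawn from baseline variables already collected in both groups, such as age, sex, type of anaemia and primary care centre.
2. Run these analyses on an extract with arms coded A/B that holds only fields common to both arms. Leave out Veri-Q readings, contact dates and symptoms from monthly visits. If the number of venous blood counts is tallied over follow-up, leave that out too, since it may point to the arm.
3. State who is blinded. If that person is neither the principal investigator nor the supervisor, amend Data Availability to match.
4. If 2 and 3 cannot be done, delete the word blinded. Step 1 is still needed, because it is the step that controls the type I error.

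The cost is a paragraph of text and a restricted extract, possibly with access for one further person. No patients are added and 138 stands. If the word is dropped, the stated property becomes less favourable, but accurate.

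### Three main result variables are times that can recur within a patient, but the named methods assume independent observations and the plan does not make the patient the unit of analysis

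*Protocol article*

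**What the plan says.** The list of main result variables under Expected results contains two counts (hospitalizations and A&E visits due to anaemia) and three times: "Time elapsed between Hb measurement and circuit activation", "Time elapsed between Hb measurement and when the transfusion is performed" and "Time elapsed between Hb measurement and return home". Nothing restricts the times to a patient's first episode or reduces them to one value per patient.

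The Intervention section sets how often the starting point of these times can occur. In one arm, "The Hb levels of participants in the intervention group will be taken once a month". The other arm has "standard monitoring, the frequency of which is variable, since it is determined by clinical criteria". In the intervention arm the transfusion circuit is activated when a reading falls below the patient's reference value, which can happen more than once. The inclusion criteria ask for at least two transfusions within a year, and the last scheduled questionnaire is at 12 months.

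The Statistical analysis section gives the univariate methods: "Univariate comparisons between the intervention group and control group will be performed using mean comparison tests (T-test or similar"), and Chi-squared or similar for distributions. It then says "Multiple linear regression will be used to model the data collected". Allocation is by patient (Assigning patients to interventions).

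**The concern.** The patient is randomised, so the patient is the independent unit. Episodes within a patient share the care team, the type of anaemia, the home situation and the day-hospital logistics, and their times are likely to be correlated. The T-test, the Chi-squared test and ordinary linear regression all treat each row of data as independent. On a file with one row per episode they would overstate the information available.

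Two things follow. Standard errors are too small, so the error rate exceeds its nominal level. Each patient is also weighted by the number of episodes, so a few frequently transfused patients can drive an arm mean, and the weighting can differ between arms because measurement frequency does.

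What is at stake is the evidence on the circuit itself. The Discussion says the study will assess the circuit and how quickly the hospital responds, and these three times are the direct measure of that. A finding of shorter times in one arm could be a false positive.

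**Working it through.** **1. The plan's own figure.** The Sample size section gives 69 per arm, from 60% versus 35% hospitalized, two-sided alpha 0.05, power of at least 80%, 10% dropout and the arcsine method.

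- h = 2·asin(√0.60) − 2·asin(√0.35) = 0.506
- n = 2·((1.960 + 0.842)/0.506)² = 61.3, rounded up to 62 per arm
- 62/0.9 = 68.9, rounded up to 69 per arm, 138 in total

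The figure reproduces. It rests on one proportion per patient, so recurring times do not touch it.

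**2. Inputs for the times.** The article gives neither the number of episodes per patient (m) nor the within-patient correlation (ICC). Both are assumptions here. I take m = 2 to 4, prompted by the entry criterion of two or more transfusions in a year, and ICC = 0.1 to 0.5.

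**3. Formula.** With m episodes per patient, the variance of an arm mean is DE = 1 + (m − 1)·ICC times what an independence analysis assumes. A nominal two-sided 5% test that ignores this has actual error 2·(1 − Φ(1.96/√DE)). Its confidence interval is 1/√DE times the correct width.

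| m | ICC | DE | Interval width relative to correct | Actual error |
|---|---|---|---|---|
| 2 | 0.1 | 1.1 | 0.953 | 6.2% |
| 2 | 0.3 | 1.3 | 0.877 | 8.6% |
| 2 | 0.5 | 1.5 | 0.816 | 11.0% |
| 4 | 0.1 | 1.3 | 0.877 | 8.6% |
| 4 | 0.3 | 1.9 | 0.725 | 15.5% |
| 4 | 0.5 | 2.5 | 0.632 | 21.5% |

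Example: m = 4 and ICC = 0.3 give DE = 1 + 3 × 0.3 = 1.9.

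**4. Check by simulation.** I used 62 patients per arm, no true difference, and episode numbers varying between patients (1 plus a Poisson count), with 3,000 replicates per setting.

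| Mean m | ICC 0 | ICC 0.1 | ICC 0.3 | ICC 0.5 |
|---|---|---|---|---|
| 2, T-test on all episodes | 4.8% | 7.1% | 10.0% | 12.3% |
| 4, T-test on all episodes | 4.7% | 9.6% | 17.2% | 25.0% |

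The rates are somewhat above the formula because episode numbers are unequal. A T-test on one mean per patient stayed between 4.5% and 5.6% in every setting run.

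**5. Limits of the range.** At ICC 0.05 the formula gives 5.6% for m = 2 and 6.8% for m = 4, so the effect can be small. At m = 12 (ICC 0.1 to 0.5) it gives 17.6% to 44.2%. That is an upper bound, because a time to activation or transfusion arises only when a low reading triggers the circuit, not at every monthly measurement.

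**The case against.** The strongest reply is that the plan never says episodes are pooled. Its sentence on the analysis set is about which participants are included, and the named tests are valid on one value per patient. A reader might infer that the p-values and intervals for these times are bound to be too optimistic. The article does not support that: it leaves the unit open, and the inflation needs both episode-level analysis and an ICC above 0. Nor are the T-test and linear regression the only methods named. Chi-squared is there too, and both tests carry an allowance for something similar. That allowance widens the choice of test but does not fix the unit.

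It can also be said that a condensed article may leave such detail to a fuller document. That has weight, but the article does choose methods and applies one regression to the collected data as a whole. Per-patient counts and recurring times need different handling, and the section as written makes no distinction.

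Three further points stand as limits:

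- The times appear in no stated objective and not in the hypothesis. Although they make up three of the five variables under that list heading, they do not threaten the main conclusion.
- Two or more transfusions is an entry history, not an on-trial rate.
- It is unclear how fully the times will be recorded in controls. The Abstract refers anaemia in either group to the circuit, while the Intervention section describes the circuit as created for the intervention. The point applies to whatever comparison between arms is made.

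**Conclusion.** The concern holds conditionally. The three times can recur within a patient, the named methods assume independence, and the patient is not fixed as the unit for them. If those methods are run on episodes, the nominal 5% error rises to about 6% to 22% by the formula, for an assumed 2 to 4 episodes per patient and ICC of 0.1 to 0.5. Intervals are then about 0.95 to 0.63 times their correct width. The true size cannot be known from the article. The comparison of hospitalizations, which is one count per patient, does not have this problem. This is worth correcting before analysis, but it is not a flaw in the trial's main comparison.

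**What to change.** In the Statistical analysis section, state that the three time variables are compared between arms with the patient as the independent unit, and choose one route in advance:

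- one summary per patient (mean or median), analysed with the tests already named; or
- a regression on the episodes with a random patient intercept or patient-clustered standard errors.

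The first route also stops patients with many episodes from dominating. Do not require a log transform: device results are almost immediate, so some times to circuit activation may be zero.

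The cost is a few lines of text, with no extra patients or data. Intervals for these three variables will be wider than a pooled-episode analysis would show, by a factor of √DE: from √1.1 = 1.05 to √2.5 = 1.58 over the assumed range. That width reflects the information actually present.
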